#### Process measures: RNT and alternative responses as habits

Two self-report measures are incorporated to assess the habitual tendency for rumination and the use of alternative processing modes. To evaluate the habitual tendency for rumination, we will include 12 items from the Habit Index of Negative Thinking (HINT; [75]), translated by the authors for this study. Additionally, the 9 items from the HINT were selected to constitute a separate measure assessing participants’ habitual use of alternative coping strategies.

### Adverse events

The intervention program used in this trial has previously demonstrated feasibility and effectiveness in preliminary studies [45, 46]. The primary aim of the self-help intervention is to enhance psychological resilience by promoting a shift from maladaptive to adaptive processing styles. However, given that the intervention requires participants to engage with and manage stressful situations, the potential for increased risk in certain participants cannot be completely ruled out. Should any adverse event occur, we will adhere to the university’s basic policy for student support, which prioritizes the physical and psychological health and safety of students. In instances where a participant exhibits a substantial increase in depressive symptomatology (e.g., a score exceeding the exclusion threshold) or heightened suicidal ideation (e.g., a score of ≥ 2 on PHQ-9 item 9), they will be promptly informed and strongly encouraged to seek immediate support from the university’s student health service center (https://www.nara-wu.ac.jp/hoken/) or student counseling center (https://www.nara-wu.ac.jp/soudan/). The contact information for these centers is provided at enrollment and reiterated at any time the participant reports an elevated level of risk. If the participant is currently under regular psychiatric care, we will also advise them to consult their treating psychiatrist as soon as possible. The principal investigator will maintain close contact with the participant to ensure that their symptom severity or suicidal risk decreases from a critical clinical level. Additionally, the principal investigator will evaluate whether the participant should continue in the study and assess the need for alternative treatment options, such as initiating or resuming regular psychiatric care. The principal investigator will convey this determination directly to the participant.

### Discontinuations

#### Discontinuation of intervention

If a participant meets any of the following criteria, the trial therapist will decide to discontinue the intervention. The participant will be invited to respond to regular assessments throughout the remainder of the study period.If the participant withdraws consent to continue with the self-help intervention.It the trial therapist considers appropriate to discontinue the study intervention from certain reasons (e.g., emergence of adverse events, serious and imminent ideation of suicide or self-harm, or other severe conditions requiring psychiatric or medical care).If the therapist considers appropriate for the participant to receive intensive face-to-face psychological or psychiatric care.

#### Discontinuation of regular assessment

If the participant withdraws consent to receive study assessment or to take part in the trial, the participant will not be contacted for further assessments and will be considered to have dropped out from the study.

### Sample size estimation

We estimated required sample size using G*power 3 [76]. Umegaki et al. [46] reported RRS mean change of *M* = 18.70 from pre- to post-intervention for RFCBT guided self-help. Therefore, we expect a slightly modest mean change of *M* = 16 for the intervention group, and, *M* = 5 for the waitlist control group (estimated from unpublished longitudinal data, reflecting natural recovery and regression to the mean). Standard deviations (*SD*) of change in RRS varies between intervention and non-intervention samples (*SD* = 14.1, 15.1; [46],unpublished data). We have based our sample size estimate on the pooled *SD* (14.5). Therefore, we estimate a between-group effect size of Cohen’s *d* = 0.75. To detect the effect size of *d* = 0.75 between RFCBT self-help and waitlist control at a two-tailed significance level of 5%, and to obtain 90% statistical power, each condition requires 39 participants. Assuming the dropout rate of 23% [46], we will recruit 51 participants into each condition.

### Statistical analysis

The main analysis will be an intention-to-treat (ITT) analysis, in which analysis is based on allocation, and based on complete case outcome data. For the main analysis, a covariate-adjusted analysis based on a general linear model, or equivalent structural equation modeling, will be conducted. This analysis will examine the primary outcome of between-group differences in rumination (RRS) 4- and 8-week post-randomization, along with secondary outcomes of between-group differences in brooding, reflective pondering, worry, depression, and anxiety. In this analysis, outcome scores at 4- and 8-week post-randomization serve as dependent variables, with measurement timing (4- vs 8-week) and condition (intervention vs control) as independent variables, and baseline scores included as covariates. Additionally, multivariate latent growth models will be used to assess whether changes in RNT predict changes in depression and anxiety. Missing data will be addressed using multiple imputation (MI) or full information maximum likelihood (FIML) method as appropriate. All statistical tests will be conducted at a 5% two-tailed significance level.

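### The main analysis is defined on complete cases under an intention-to-treat label, while MI or FIML is promised without saying for which analysis, so the primary RRS result is not uniquely defined

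*Protocol article*

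**What the plan says.** All of this is in the protocol article. Statistical analysis makes the main analysis intention-to-treat, "in which analysis is based on allocation, and based on complete case outcome data". The model is open between two forms: "a covariate-adjusted analysis based on a general linear model, or equivalent structural equation modeling, will be conducted". Two visits enter it: "outcome scores at 4- and 8-week post-randomization serve as dependent variables", with baseline as covariate. The paragraph then introduces multivariate latent growth models for the question whether change in repetitive negative thought predicts change in symptoms. The next sentence reads "Missing data will be addressed using multiple imputation (MI) or full information maximum likelihood (FIML) method as appropriate".

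Sample size estimation expects material loss ("Assuming the dropout rate of 23" per cent) and recruits 51 per arm to keep 39. Discontinuation of intervention says that participants who stop the intervention are still invited to assessments. Discontinuation of regular assessment counts as dropouts those who withdraw from assessment or from the trial.

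**The concern.** An analysis restricted to complete outcome data has no missing outcomes left to impute, and an MI or FIML analysis of everyone randomized is not a complete-case analysis. The paragraph states both and does not say which one yields the primary RRS comparison.

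The permitted model forms widen the gap. With full follow-up, the linear model and the SEM can be equivalent. With missing follow-up, a linear model that deletes incomplete records and an SEM fitted by FIML use different participants and need not agree.

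The label matters too. Leaving out randomized students because of something that happened after randomization is not intention-to-treat without qualification. The arms also differ in their reasons to stay: one has workbooks, in-person sessions and vouchers, and the other waits eight weeks. A dropout mechanism that differs by arm therefore cannot be dismissed, and that is the case in which the two approaches part.

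**Working it through.** **Inputs from the protocol article (Sample size estimation, Statistical analysis).** Expected changes: "we expect a slightly modest mean change of *M* = 16 for the intervention group, and, *M* = 5 for the waitlist control group", a difference of 16 − 5 = 11 points. SD of change 14.5. Effect size 0.75 (11/14.5 = 0.76, stated as 0.75). Two-sided 5%, power 90%, dropout 23%, 1:1 allocation.

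**Step 1: the plan's own figure.** A two-sample t-test (noncentral t) with d = 0.75 gives 39 per arm, power 0.905. Dropout: 39/(1 − 0.23) = 50.6, so 51 per arm and 102 in total. Both figures reproduce, and the sample size is not in question.

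**Step 2: the two analysis sets.** Complete-case: 102 × 0.77 = 78.5, about 78 students. Left out: 102 × 0.23 = 23.5, about 23 to 24. MI or FIML on all randomized: 102. With no missing data, 51 per arm would have power 0.963, which is an upper bound for MI or FIML and not its expected power.

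**Step 3: can the estimates differ?** The following inputs are assumed and not in the documents:
- mean changes of −10.5 and −16 (intervention) and −5 and −5 (waitlist) at weeks 4 and 8, so half the effect is present at week 4;
- SD 14.5 at both visits, with correlation ρ = 0.65 between the week-4 and week-8 changes;
- 23% lost between weeks 4 and 8 in each arm, all with a week-4 score;
- where dropout depends on the score, a log-odds slope of 0.5 or 1 per SD of poorer week-4 change relative to the arm's own mean (odds ratios e^0.5 = 1.65 and e^1 = 2.72).

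In an arm where dropout depends on the week-4 change, the complete-case week-8 mean shifts by

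shift = ρ × SD × (mean standardised week-4 deviation among those who stay).

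With the intercept set to give 23% dropout, that mean deviation, evaluated numerically, is −0.111 at slope 0.5 and −0.197 at slope 1. Hence 0.65 × 14.5 × (−0.111) = −1.05 and 0.65 × 14.5 × (−0.197) = −1.86 points.

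Size of the week-8 difference (truth 11), from large-sample simulation:

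| Where dropout depends on the week-4 score | Complete-case, slope 0.5 | Complete-case, slope 1 | Likelihood using week 4 |
|---|---|---|---|
| Neither arm | 11.0 | 11.0 | 11.0 |
| Both arms alike | 11.0 | 11.0 | 11.0 |
| Intervention arm only | 12.0 | 12.9 | 11.0 |
| Waitlist arm only | 10.0 | 9.1 | 11.0 |

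The one-arm rows are 11 ± 1.05 and 11 ± 1.86, up to rounding and simulation error.

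**Step 4: a check at the trial's size with baseline adjustment.** This used 4,000 simulated trials of 51 per arm, with assumed baseline-to-follow-up correlation 0.5, week 4 to week 8 correlation 0.7 and slope 1. With dropout dependent in the intervention arm only, complete-case ANCOVA averaged 12.3 and FIML 11.0, a gap of 1.3 points against a standard error of about 2.9. Under random dropout both averaged 11.0, with standard errors 2.91 (complete-case) and 2.80 (FIML).

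**The case against.** The strongest reply is that the paragraph is unclear, not self-defeating. The MI/FIML sentence directly follows the latent growth models, where FIML is a usual choice, or it may describe a sensitivity analysis. Sizing for 39 evaluable per arm fits complete-case as the intended main analysis. This reading is possible, but the text does not state it. Even if it is right, a sentence is needed to say so, and the intention-to-treat label needs qualifying.

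It is also fair that stopping the intervention does not by itself make outcomes missing, because assessments continue. The documents do not say whether the 23% taken from the pilot study counts stopped treatment or missing outcomes, so true outcome loss may differ.

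A reader might infer three stronger things that the documents do not support:
- That complete-case inflates the benefit by 10 to 17%. That holds only if dropout depends on outcome in the intervention arm and is random in the waitlist arm. The reverse case understates the benefit, and the same mechanism in both arms gives no bias. Nothing in the documents favours one of these.
- That the choice of method stays open until the data are seen. The article leaves MI or FIML to be chosen as appropriate. An analysis plan that is not shown may settle it.
- That observed week-4 scores will be discarded. The article does not say whether a complete case needs both visits or either one.

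**Conclusion.** The concern holds as an unreconciled definition of the primary analysis. One paragraph fixes complete-case data for the main analysis and also promises MI or FIML for an unnamed analysis. This goes beyond detail that an article leaves to the analysis plan: taken literally, the stated rule drops about 23 to 24 of 102 randomized students under an intention-to-treat label.

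The two approaches can give different answers; they need not. Under the assumptions listed, the complete-case error runs from about 1.9 points too small to 1.9 points too large on an 11-point difference, and is nil when dropout is random or acts alike in both arms. In the adverse cases it is smaller than the roughly 2.9-point standard error of one trial, but it is systematic. The likelihood result stays at 11 because dropout was assumed to depend only on observed scores and every dropout had a week-4 score. Loss before week 4, or dropout that depends on unobserved scores, would weaken that protection.

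**What to change.** In Statistical analysis, delete the second half of "in which analysis is based on allocation, and based on complete case outcome data", from the comma on. Name one primary method: a likelihood-based repeated-measures model, or the equivalent SEM fitted by FIML, with baseline, 4-week and 8-week RRS, including all randomized participants as allocated. Label complete-case as a sensitivity analysis and define whether it needs both visits or either one. Say which analyses the MI/FIML sentence covers. A delta-adjusted MI is an optional further sensitivity analysis.

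The cost is small because the plan already allows SEM and FIML: no new data and one extra sensitivity run. The real cost is a protocol and registry amendment in a trial that has been recruiting since January 2024 and whose interim outcome results go to the authors. The amendment should be dated and should state whether interim outcome results had been seen, so that the change cannot be taken as data-driven.

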**Methods:**

This study is a single-site, assessor-blinded, parallel-group, two-arm randomized controlled trial (guided self-help vs. waitlist), employing block randomization in a 1:1 ratio. A total of 102 female university students with elevated levels of RNT will be recruited. Participants will be randomly assigned to either the intervention group receiving guided RFCBT self-help, or the waitlist control group. The primary outcome is rumination, assessed using the Ruminative Responses Scale. Measurements will be conducted at 4- and 8-week post-randomization.

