### The current study

The present study aims to evaluate the effectiveness of a culturally-adapted, workbook-based RFCBT guided self-help intervention within an RCT design. Our study, the RESUME-CBT (Resilience through Emotional Support for University Mental well-being and Empowerment through CBT) trial, is a single-site, assessor-blinded, parallel, two-arm, block randomized controlled trial, assessing the effectiveness of culturally-adapted RFCBT guided self-help in reducing RNT and symptoms of depression and anxiety post-intervention, compared to a waitlist control. A waitlist control group, which attempts to control for the passage of time and repeated assessment in the target population [52], was implemented to address the methodological limitations of our earlier studies. In those investigations, the effectiveness of the Japanese version of RFCBT guided self-help had been evaluated solely within a single-group design [45, 46], thereby limiting our ability to disentangle true intervention effects from spontaneous improvements or regression to the mean (but see Furukawa et al. [53], for evidence indicating that waitlist groups may represent a suboptimal control condition).

Given that RNT is an established risk factor, this trial examines whether guided RFCBT self-help intervention can reduce RNT among young Japanese adults at high risk for RNT (i.e., female university students), and thus reduce symptoms of depression and anxiety. In other words, our trial serves as a proof-of-concept study exploring the potential of RFCBT in targeting rumination and worry within a Japanese population.

Additionally, we will investigate whether changes in RNT predict subsequent changes in symptoms of depression and anxiety. A recent meta-analysis suggests that rumination-focused CBTs reduce rumination, thereby alleviating depressive symptoms [35]. However, data are insufficient to conclude definitively that rumination-focused CBTs reduce depression (and/or anxiety) by decreasing RNT. This study thus aims to address this evidence gap.

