Reductions in RNT following RNT-focused cognitive-behavioral interventions are associated with symptomatic improvement [34, 35]. However, empirical evidence demonstrating that symptom reduction is a consequence of diminished rumination remains limited [35]. The present study will advance theoretical understanding of rumination as a central risk factor for depression and anxiety by examining its role as a psychopathological mechanism that exerts a causal influence on these conditions.

Additionally, it is crucial to explore whether RFCBT can be effectively delivered as a guided self-help intervention through a workbook format. Although RFCBT has been administered via guided online self-help formats [38, 78], no study has yet examined its effectiveness in a workbook format. This study aims to evaluate the effectiveness of this previously untested mode of delivery.

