### Strengths and limitations

This study has several limitations. Although RFCBT guided self-help has demonstrated promising results in reducing RNT as well as depressive and anxiety symptoms in Japanese samples, these findings were derived from single-case designs [45, 46]. To delineate true intervention effects from spontaneous improvement or regression to the mean, the present study therefore incorporates a waitlist control condition. While comparisons between the self-help and waitlist conditions enable us to ascertain whether observed effects reflect genuine therapeutic benefit rather than spontaneous remission, and although waitlist controls remain widely used in clinical trials evaluating psychological interventions [52], some evidence suggests that waitlist conditions may exert detrimental effects [53]. Accordingly, once intervention effects are established within our design, future studies may profit from employing no-treatment or non-specific control conditions.

Because our primary objective is to detect intervention-related change, this trial employs a pre-post design that assesses relatively short-term outcomes (4- and 8-week post-randomization). However, to determine whether reductions in RNT meaningfully protect participants from future depressive episodes, longer-term follow-up assessments are essential. Subsequent studies should evaluate whether treatment gains are sustained over extended periods following the termination of the intervention.

Third, our sample size was calculated based on expected between-group differences; thus, additional multivariate latent growth analyses are insufficiently powered. Fourth, the single-site design may increase the risk of sampling bias.

Despite these limitations, the study possesses notable strengths. To our knowledge, this is the first adequately powered RCT to evaluate the effectiveness of RFCBT in reducing RNT in a non-Western population. Prior to the trial, the content and delivery of the guided self-help program were refined and substantiated through preliminary case-series studies [45, 46], enhancing the likelihood that the intervention would be effective in our target population.

University students in Japan, as well as in other countries, are experiencing a mental health crisis. Demonstrating that high-risk students with elevated RNT can be effectively supported would represent a critical step toward improving the mental health of this vulnerable population.

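### The protocol aims to show that RNT change precedes symptom change and acts causally, but the only analysis named for this is a latent growth model with no lag stated, which in its standard form shows concurrent association only

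*Protocol article*

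**What the plan says.** Under The current study, the protocol article gives the aim with a time order: "we will investigate whether changes in RNT predict subsequent changes in symptoms of depression and anxiety". It motivates this by noting that "data are insufficient to conclude definitively that rumination-focused CBTs reduce depression (and/or anxiety) by decreasing RNT", and says the study aims to address that gap. The Discussion goes further and says the trial will advance understanding of rumination by "examining its role as a psychopathological mechanism that exerts a causal influence on these conditions".

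Statistical analysis names one method for this question: "multivariate latent growth models will be used to assess whether changes in RNT predict changes in depression and anxiety". The idea of *subsequent* change does not appear there. No lag, piecewise segment, cross-lagged path or latent-change-score model is named.

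On timing, the abstract states "Measurements will be conducted at 4- and 8-week post-randomization", and Statistical analysis has "baseline scores included as covariates". RNT and symptoms are therefore measured together at three waves: 0, 4 and 8 weeks.

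Strengths and limitations makes one concession about this analysis, that "additional multivariate latent growth analyses are insufficiently powered".

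**The concern.** The aim is about order (RNT first, symptoms afterwards) and the Discussion is about cause. A growth model summarises each construct by its trajectory over the whole observation period. If both trajectories cover the same 0–8 weeks, an association between them says that people whose rumination fell more also had symptoms that fell more. It does not say which fell first.

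A positive result would then be equally compatible with symptoms driving rumination, or with both self-reports falling together. It could nevertheless be reported as evidence on mechanism, because the protocol has announced it that way. The stated limitation does not cover this: a larger sample would sharpen the estimate of the association but would not give it a direction.

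Cause is a further step. Randomisation protects the effect of arm on RNT and the effect of arm on symptoms. It does not protect the path from RNT change to symptom change, which remains open to confounding.

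**Working it through.** **Plan's own figures.** None is given for the growth-model analysis. The sample size (39 per arm; 39 / (1 − 0.23) = 50.6, so 51 per arm) concerns the between-group comparison. It reproduces and is not in question.

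**Inputs.** Waves at 0, 4 and 8 weeks, from the abstract and Statistical analysis. The model class is from Statistical analysis. *Assumed, because the article does not state it:* linear growth, equal residual variances, one slope per construct, and arm and intercepts predicting both slopes.

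**Step 1: what the slope measures.** The least-squares slope weight at time t is (t − mean) / sum of (t − mean)².
- The mean time is 4, the deviations are −4, 0 and +4, and the sum of squares is 32.
- The weights are −4/32 = −0.125, 0/32 = 0, and +4/32 = +0.125.

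The slope is the 0–8 week change divided by 8. The 4-week score, the only source of order within follow-up, has zero weight.

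**Step 2: can fit distinguish the two directions?** Given arm and intercepts, the two slopes have a 2×2 covariance matrix with three free elements. Either regression direction also has three parameters: one coefficient, one predictor variance and one residual variance. Illustrative values are variance 1 for the RNT slope, 1.5 for the symptom slope, and covariance 0.4.
- Symptom slope on RNT slope: coefficient 0.4/1 = 0.4; residual 1.5 − 0.4² × 1 = 1.34. Implied covariance 0.4 × 1 = 0.4; implied symptom variance 0.16 + 1.34 = 1.5.
- RNT slope on symptom slope: coefficient 0.4/1.5 = 0.267; residual 1 − 0.4²/1.5 = 0.893. Implied covariance 0.267 × 1.5 = 0.4; implied RNT variance 0.107 + 0.893 = 1.

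Both directions return the same matrix, so fit cannot choose between them. This does not depend on the values used.

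**Step 3: three opposing orders, one slope correlation.** Give each construct an early (0–4) and a late (4–8) change, each with variance 1, early and late changes within a construct being independent. The variance of each 0–8 week change is then 1 + 1 = 2, and the slope correlation is the total cross-covariance divided by 2.
- RNT leads (early RNT to late symptoms, 0.6): 0.6/2 = 0.30.
- Symptoms lead (early symptoms to late RNT, 0.6): 0.6/2 = 0.30.
- Concurrent (0.3 in each half): (0.3 + 0.3)/2 = 0.30.

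A simulation of 200,000 people under these assumptions gave:

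| Scenario | Slope correlation | RNT 0–4 with symptoms 4–8 | Symptoms 0–4 with RNT 4–8 |
|---|---|---|---|
| RNT leads | 0.303 | 0.60 | 0.00 |
| Symptoms lead | 0.301 | 0.00 | 0.60 |
| Concurrent | 0.299 | 0.00 | 0.00 |

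The slope correlation does not separate the three scenarios. The lagged contrasts do, and they need only the waves already planned.

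**The case against.** The strongest reply is that this faults a specification the article never states. Statistical analysis fixes neither the growth shape, nor the slope window, nor the handling of arm. A piecewise or latent-change-score variant is possible with these three waves and may sit in a statistical analysis plan that is not shown. That stands as a limit on the point: the 0–8 week window is inferred, and the absence of path detail is not itself the finding. What remains is that the aim specifies an order, the one method named in its usual form does not test that order, and the causal wording in the Discussion stands whatever a further document says.

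A reader might infer that the planned model carries no directional information whatever. The documents do not support that. The equivalence in Step 2 holds for the otherwise saturated slope-on-slope form. It can fail under restrictions such as omitting a direct path from arm to symptom slope, which assumes full mediation; a path from baseline RNT level to symptom slope is also ordered in time. Statistical analysis neither states nor excludes these.

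The Discussion also announces an examination, not a causal finding, and the protocol says it aims to address the evidence gap, not that it will close it. The limitations call for longer follow-up to judge protection against future episodes, which restrains some claims about later symptoms but not this one. Finally, the analysis is introduced as additional and lies outside both formal hypotheses. This bears on how much the point matters, not on whether it is right.

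**Conclusion.** The point holds as a mismatch between aim and named method. In the standard linear parallel-process form, with arm and intercepts predicting both slopes, the planned analysis would show concurrent association between RNT change and symptom change over 0–8 weeks, not temporal order. Because RNT change is not randomised, a causal reading would not follow even from a lagged model.

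The conclusion rests on the assumed form of the growth model. The 0.30 and 0.60 figures are illustrations from assumed unit-variance changes, not predictions for this trial; the equivalence of the two directions does not depend on them.

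Two stronger readings should be avoided. The growth model need not be discarded: it is a reasonable description of joint change for an additional analysis. Nor does the protocol concede low power for a mediation analysis: it names none, and its concession is about the latent growth analyses. The primary and secondary efficacy comparisons, the sample size and the data collection are unaffected. The change is worth making because it is cheap and because, without it, a direction could be chosen after the results are seen.

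**What to change.** Keep the growth model and do one of the following, prespecified and labelled exploratory:

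1. Add a lagged model: 8-week PHQ-9 and GAD-7 on 4-week RRS and PSWQ, adjusted for 4-week and baseline symptoms, baseline RNT and arm. Report the reverse path (4-week symptoms to 8-week RNT) alongside.
2. Specify the growth model as piecewise or as latent change scores, with RNT change over 0–4 weeks predicting symptom change over 4–8 weeks.

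In either case, reword the Discussion from causal influence to a temporal association consistent with a mechanism. Add to Strengths and limitations that temporal order is only weakly addressed and that the mediator is not randomised.

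**Cost.** No new data, but a softer claim. Option 1 adds up to 2 × 2 × 2 = 8 exploratory paths (two RNT measures, two symptom measures, two directions), all underpowered. Week 4 may also fall mid-treatment: four workbooks at 1–2 weeks each take 4 × 1 = 4 to 4 × 2 = 8 weeks, so the early RNT change may reflect only part of the programme. Both caveats should be stated with the results.

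### The stated mechanism analysis relates RNT change to symptom change and names no condition effect or indirect effect, so by itself it cannot show whether RFCBT lowers depression or anxiety by lowering RNT

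*Protocol article*

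**What the plan says.** The Protocol article, under The current study, gives the motive for the mechanism work: "data are insufficient to conclude definitively that rumination-focused CBTs reduce depression (and/or anxiety) by decreasing RNT". It says the trial aims to address that gap. The Discussion returns to the point, noting that "empirical evidence demonstrating that symptom reduction is a consequence of diminished rumination remains limited", and says the study will examine rumination as a mechanism acting causally on depression and anxiety.

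The analysis offered for this is one sentence under Statistical analysis: "multivariate latent growth models will be used to assess whether changes in RNT predict changes in depression and anxiety". The same paragraph lists condition, measurement time and baseline score as terms of the main model. It lists no terms for the growth model and names no indirect effect.

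Strengths and limitations says the growth analyses are insufficiently powered. Neither the primary nor the secondary hypothesis covers them.

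**The concern.** Whether RFCBT lowers symptoms by lowering RNT is a question about an effect of the randomised condition that passes through RNT. Whether RNT change predicts symptom change is a question about how two changes go together across students. The second can be answered yes when the answer to the first is no, because stress, term time or regression to the mean can move both measures in students whom the intervention did not help.

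A significant association would thus be reported against an aim that it does not address. The concern is separate from the time order of the changes: a correctly lagged association without condition would have the same gap.

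**Working it through.** **Sample size, to fix n.** Sample size estimation gives expected changes of 16 and 5 and a pooled SD of 14.5, so d = (16 − 5)/14.5 = 0.759, which the plan takes as 0.75. The plan states that "to obtain 90% statistical power, each condition requires 39 participants". A two-sample t test (noncentral t) at two-sided 5% and d = 0.75 also gives 39 per arm, with power 90.5%. With 23% dropout, 39/0.77 = 50.6, so 51 per arm. The plan's figures reproduce: 78 completers, 102 recruited.

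**Aim against stated target.**

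| Place | What it is about |
|---|---|
| The current study | Whether the therapy reduces symptoms by decreasing RNT |
| Discussion | Symptom reduction as a consequence of reduced rumination |
| Statistical analysis, main model | Effect of condition on each outcome |
| Statistical analysis, growth model | RNT change predicting symptom change |

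The last row contains no quantity that would be zero if RFCBT did nothing.

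**Simple change-on-change test, inert RFCBT.** Let r be the correlation of individual changes (an assumption, as none is given). The test level follows the plan: "All statistical tests will be conducted at a 5% two-tailed significance level". The Fisher approximation is

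P(significant) = 1 − Φ(1.96 − m) + Φ(−1.96 − m), with m = atanh(r) × √(n − 3).

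For n = 78, √75 = 8.660:

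- r = 0.2: m = 0.2027 × 8.660 = 1.756, P = 42%
- r = 0.3: m = 0.3095 × 8.660 = 2.681, P = 76%
- r = 0.4: m = 0.4236 × 8.660 = 3.669, P = 96%

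At r = 0.1 the figure is 14%. It passes 50% at r = tanh(1.96/8.660) = 0.22. With n = 102 the figures at 0.2, 0.3 and 0.4 are 52%, 87% and 99%.

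**Latent growth model, inert RFCBT.** This is closer to the stated method. The simulation used a bivariate model with three waves (baseline, weeks 4 and 8), n = 78, and a likelihood-ratio test of the slope-slope covariance. Assumed values: intercept variance 1, slope variance 0.25 or 0.5, residual variance 0.25, within-wave residual correlation 0.3.

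| Latent slope correlation | Residual covariance modelled | Residual covariance left out |
|---|---|---|
| 0 | – | 31–45% |
| 0.3 | 15–22% | 71–82% |
| 0.5 | 18–46% | 94–95% |

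Each cell has 120 to 150 runs, so about ±9 points. A repeat of the modelled column with 300 runs per setting gave 10–21% at 0.3, 20–43% at 0.5 and about 7% at 0. It agrees within simulation error, and the bottom of the range is the least secure part.

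**Joint test with condition.** This requires both condition → RNT change, and RNT change → symptom change adjusted for condition, to be significant. With inert RFCBT, n = 78 and r from 0.2 to 0.6, it was significant in 1.6% to 6.0% of 2,000 runs per setting.

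**Limit of that repair.** Suppose RFCBT moves RNT by d = 0.75 and does nothing to symptoms, which merely share causes with RNT. The joint test was then still significant in 38% to 91% of runs for r from 0.2 to 0.6, while the total effect of condition on symptoms was significant in about 5%.

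**The case against.** **Silence is not exclusion.** A reader might infer that the growth model leaves the treatment arm out. The article does not say so. It gives one sentence on a supplementary model, and a full analysis plan may well include condition. This stands as far as it goes, so the point is not a missing model detail. What remains is that the article states both an aim and the quantity to be tested, and the two differ.

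**The result would usually be significant even if RFCBT did nothing.** This stronger reading is tempting but not supported. It needs a correlation of changes that the protocol does not give. The coefficients of 0.56 to 0.61 under Outcome measures are cross-sectional validity figures against several scales and cannot stand in for it. In the growth model with residual covariance modelled, the rate stayed below half at slope correlations of 0.3 and 0.5.

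**An inert intervention would show elsewhere.** The main model already tests condition on rumination and on symptoms, and the low rate of the joint test mostly reflects its condition-to-RNT component. This is fair: null main results would stand beside the association. Nothing in the text, however, makes reading the association depend on them, and even where RFCBT works the association does not estimate how much of the effect passes through RNT.

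**Low power is already conceded.** That warns of missing a real association. It does not warn that a significant one would leave the question open.

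**Conclusion.** The concern holds as a mismatch between aim and analysis. The stated association does not depend on RFCBT having worked. With an inert intervention and 78 completers it can be significant more often than 5% of the time: about 42% to 96% for a simple change test at an assumed correlation of 0.2 to 0.4, and about 15% to 46% in a growth model with residual covariance modelled at an assumed slope correlation of 0.3 to 0.5. The rates rest on assumed correlations and variances, so only the direction is firm.

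A reader might also infer that adding condition would license the Discussion's causal wording. It would not: the joint test was often significant when RNT and symptoms only shared causes. The analysis is supplementary, but it is the only one serving a declared aim, so it should be corrected.

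**What to change.** Under Statistical analysis, enter condition as a predictor of both RNT change and symptom change, and name the indirect effect (condition to RNT change to symptom change), with a bootstrap interval, as the mechanism estimate. Label it exploratory, in line with the power caveat already given. State that it assumes no unmeasured common causes of RNT change and symptom change, and report it beside the total effect of condition on symptoms. If this is not wanted, reword The current study and the Discussion to claim an association only.

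The cost is two paths and one derived parameter in a model already planned, or a few sentences. The downside is a wider interval and a lower chance of significance. With d = 0.75 on RNT, true mediation and n = 78, the joint test was significant in 39%, 67% and 87% of runs at r = 0.2, 0.3 and 0.4, against 47%, 80.5% and 97% for the plain association. No new data are needed, and the primary comparison and sample size do not change.
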